### Household-level intervention

Aside from the village-level intervention, additional household-level intervention is very important in the context of the RCT design. Social support may modulate adherence to TB medication protocols; we will thus collect household-level data. Because TB is highly infectious, it is not rare that more than one member of a household will become infected. It is important to be prepared for this situation by collecting relevant data in the initial questionnaire. However, interaction between members of a household will influence the groups’ results. To solve this problem, a great deal of work is necessary to better inform the patients and their families of the treatment regime. Furthermore, following up patients is extremely important. Once a member of the household is infected, chemotherapy treatment is necessary. Finally, it is important to educate the family members on nutrition, exercise, and proper household ventilation.

### Individual-level interventions

Patients in the intervention group will undergo an interactive training course before the research commences. The course will cover bracelet design and application, early symptoms of TB, routes of TB transmission, effects of TB on relatives, TB treatment strategies, the importance of adhering to medication regimens, how to prevent TB, medication side effects, how to open the bracelet, how to switch on the power, how to use a smartphone to download the application, and how to communicate with the village physicians using the application. The course will run for three 90-min sessions. The primary objective will be to encourage patients with TB to take responsibility for their treatment.

After completing the course, the patients will visit their village physicians monthly for medical check-ups and to receive their TB medication for the next month. The village physicians will also check the bracelet power and address any concerns of the patients.

Each day, the patients will photograph themselves taking their medication using a smartphone; these photographs will be automatically sent to the control center, where the photographs will be assessed. TB patients in the interventional group will receive TB-relevant education from the research term, delivered via the smartphones. Patients with TB in the control group (thus, not following the BSDOT strategy) will be treated according to WHO recommendations; a physician must observe the ingestion of TB treatment pills on 6 days per week. Otherwise, patients in the control group will not receive any additional intervention. Research staff will record the following baseline factors: sociodemographic characteristics including age, sex, socioeconomic status, educational level, marital status, and health behaviors (smoking or drinking status). These baseline data will be used to test the accuracy of randomization and to control for confounding effects on primary and secondary outcomes. The patients in the control group also receive TB education, although it generally comes from village physicians or media sources such as newspaper articles or television broadcasts. Pill consumption frequencies by control groups will be assessed by the village physicians during the 2-week follow-up visits. Some drugs may cause adverse effects such as such as vomiting and diarrhea. Any reports of such conditions require careful analysis; it may be possible to adjust the drug dosage or to avoid taking medication on an empty stomach. Also, it may be useful to regularly measure liver and kidney functions. Treatment may be terminated if the adverse effects are very severe. However, prior to study commencement, patient education in terms of drug effects, dose susceptibilities, and possible adverse effects is essential

### Recruitment

The village physicians treating patients in both groups will be trained to collect and report all new and previously treated drug-sensitive cases of TB. Our research staff (who have professional medical knowledge) will be trained on the protocols and procedures of the study and will initially contact eligible patients after (1) village physicians identify patients who meet the study criteria, (2) eligible patients have been contacted by telephone, (3) patient eligibility has been confirmed, (4) the research project has been explained to patients with TB by telephone, patient consent has been gained, and contact information recorded, and (5) interviews have been arranged between patients with TB and other research staff. The research staff will also ask patients about their smartphone usage and the number of smartphones in the household. The average duration of the continuation phase of drug-sensitive TB treatment will be about 6 months.

### Sample size

Sample size calculations were based on a cluster randomized trial; the endpoint was the nonrecovery rate at the end of the trial. Assuming seven clusters per arm, a two-sided type-I error of 5%, a type-II error of 10%, and a percentage with nonadherence in the control arm of 30%, an intra-cluster correlation coefficient (ICC) of 0.1 was estimated as a mid-range value from a list of ICCs from similar studies in terms of intervention targets, outcomes, and units of randomization. Using a treatment effect size of a 0.15 increase in the proportion of successful treatments over the 0.78 successful treatment rate for usual care, based on published local treatment success rates and findings of studies with a smartphone as a facilitator of adherence in similar settings, 1300 TB patients would be required to detect a 40% reduction in the endpoint in the intervention arm with an alpha of 0.05, power of 90%, and coefficient of variation of 0.25. The sample size was adjusted to 1365 assuming 5% missing endpoint data.

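### With the stated seven clusters per arm and ICC of 0.1, 90% power cannot be reached at any sample size for any stated effect, and a between-cluster CV of 0.25 would contradict that ICC

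*Protocol article*

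**What the plan says.** All the inputs are in the Sample size section of the protocol article. It assumes a cluster randomised trial: "Assuming seven clusters per arm, a two-sided type-I error of 5%, a type-II error of 10"%. On clustering it says that "an intra-cluster correlation coefficient (ICC) of 0.1 was estimated as a mid-range value". The endpoint is named as nonrecovery at the end of the trial, but the control rate is given as "a percentage with nonadherence in the control arm of 30"%. The next sentence uses a different pair, a rise of 0.15 from a usual-care success rate of 0.78. It concludes that "1300 TB patients would be required to detect a 40% reduction in the endpoint in the intervention arm". The target power is again put at 90%, and a second variability figure is added, a "coefficient of variation of 0.25". The 1300 is then raised to 1365 for 5% missing endpoint data. The text does not say whether 1300 is a total or a number per arm, or what the coefficient of variation refers to.

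The Study sites section (Phase 3) lists seven counties in total and says that the patients chosen in each county go to both groups. The legend of Fig. 2 calls these counties the seven clusters.

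**The concern.** With few clusters and a sizeable ICC, adding patients to the same clusters soon stops adding information. Seven clusters per arm with an ICC of 0.1 is such a case, so 90% power from 1300 patients looks implausible at sight. Two parameters, an ICC and a CV, also appear to describe the same clustering with incompatible values.

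At stake is how the result will be read. A trial reported as having 90% power invites the reader to take a null result as evidence against the effect. If the stated ICC is right and the true effect is the stated 40% reduction, power is well below one half, and a null result would say little.

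**Working it through.** **Inputs (Sample size section).** c = 7 clusters per arm; two-sided alpha 0.05; power 90%; ICC 0.1; CV 0.25; N = 1300. The text supports three effects on the non-success scale: 22% to 7% (success 0.78 to 0.93), 30% to 18% (40% reduction from 30%) and 22% to 13.2% (40% reduction from 22%).

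**Trying to reproduce 1300.** Using the ICC of 0.1 with seven clusters per arm, no version gives 1300 at 90% power. The variants tried were one- and two-sided tests, with and without continuity correction, and 1300 as total or per arm. The nearest match drops the ICC and treats 0.25 as the between-cluster CV, k. Without the customary extra cluster, c = 10.507 × [(p0q0 + p1q1)/m + k²(p0² + p1²)]/(p0 − p1)². For 30% to 18% and c = 7 this gives m = 184 per cluster, so 7 × 184 = 1288 per arm.

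**Independent patients needed per arm.** n = (1.96 + 1.2816)² × (p0q0 + p1q1)/(p0 − p1)², with (1.96 + 1.2816)² = 10.507:
- 22% to 7%: 10.507 × 0.2367/0.0225 = 111
- 30% to 18%: 10.507 × 0.3576/0.0144 = 261
- 22% to 13.2%: 10.507 × 0.2862/0.007744 = 388

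Pooled-variance formulas give 114, 265 and 392.

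**Ceiling.** Effective size per arm is cm/[1 + (m − 1)ICC], which tends to c/ICC = 7/0.1 = 70 as m grows. All three requirements exceed 70, so no number of patients is enough. At an ICC of 0.1, 90% power needs more than n × 0.1 clusters per arm, that is 11.1, 26.1 and 38.8, whatever the cluster size.

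**Power with the ICC.** For 1300 in total, m = 1300/14 = 92.9, the design effect is 1 + 91.9 × 0.1 = 10.19, and the effective size is 650/10.19 = 63.8 per arm. For 1300 per arm, m = 185.7, the design effect is 19.47, and the effective size is 66.8. The standard error is √[(p0q0 + p1q1)/effective n]. Each cell is normal approximation / noncentral t with 14 − 2 = 12 df.

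| Effect | 1300 total | 1300 per arm | Unlimited patients |
|---|---|---|---|
| 22% to 7% | 69% / 62% | 71% / 64% | 73% / 66% |
| 30% to 18% | 36% / 31% | 37% / 33% | 39% / 34% |
| 22% to 13.2% | 26% / 23% | 27% / 24% | 28% / 24% |

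Enrolling 1365 moves none of these by as much as one percentage point. If 0.25 is instead the variation in cluster size, the design effect is 1 + (1.0625 × 92.9 − 1) × 0.1 = 10.77, and power at 1300 in total falls slightly, to 67% / 60%, 34% / 30% and 25% / 22%.

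**ICC against CV.** On the non-success scale k = √[ICC(1 − p)/p]. An ICC of 0.1 implies k = 0.48 at 30% and 0.60 at 22%. Conversely, k = 0.25 implies an ICC of 0.0625 × 0.30/0.70 = 0.027 or 0.0625 × 0.22/0.78 = 0.018.

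**Power with k = 0.25 in place of the ICC.** Variance per cluster pair = (p0q0 + p1q1)/m + k²(p0² + p1²), divided by 7:
- 30% to 18%: 84% / 78% at 1300 in total; about 90% / 85% at 1300 per arm
- 22% to 13.2%: 78% / 71% at 1300 in total
- 22% to 7%: over 99% by either method

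**Effects.** Non-success from 22% to 7% is a reduction of 0.15/0.22 = 68%, not 40%, and a control rate of 30% does not agree with 1 − 0.78 = 22%.

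**The case against.** The strongest reply is that 1300 came from the CV and that the ICC is a stray sentence. Much of this stands. With k = 0.25, 30% to 18% and 1300 read as per arm, power is 90% by the normal approximation, close enough to suggest that this is how the number arose. A reader might infer that no combination of the stated inputs gives 90% power at 1300. That is not so: this combination does, and k = 0.25 with success 0.78 to 0.93 gives over 99%. But both set aside an ICC that the paragraph states outright. The first also needs a per-arm reading that the text does not give and omits the customary extra cluster; with t it gives 85%.

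A reader might also conclude that a null result is the likely outcome. That follows only for an ICC of 0.1 together with a 40% reduction (23% to 36%). With success 0.78 to 0.93, or with k = 0.25, power is above one half.

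Finally, the figures might be taken as the power of the trial itself. The documents do not support that. If each of seven counties contains both arms, as the Study sites section says, the design effect for parallel clusters and the ceiling of 70 do not describe the design. They check the Sample size paragraph only.

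**Conclusion.** The paragraph is wrong as written. Its seven clusters per arm, ICC of 0.1 and 90% power are incompatible for every effect it states, at any sample size and whether 1300 is total or per arm. At 1300 in total the power is 26% to 69% by the normal approximation, or 23% to 62% by t with 12 df, the range in each case being across the three effects. The ceiling assumes 14 parallel clusters and a common ICC of 0.1; the power figures also assume equal cluster sizes.

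If 0.25 is the between-cluster CV on the nonrecovery scale, it contradicts the ICC by a factor of about four to six (0.1/0.027 to 0.1/0.018). The document does not define it, so which of the two was intended cannot be settled from the text. Nor can one correct power be given until the control rate and the effect are fixed.

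**What to change.** Rewrite the Sample size paragraph so that it:
- keeps one clustering parameter, ICC or CV, and defines it
- uses one endpoint, one control rate (30% or 22%) and one effect (a 40% reduction, or 0.78 to 0.93)
- says whether 1300 is a total or per arm
- names the randomised unit and agrees with the Study sites section on seven counties in total or seven clusters per arm, and on whether a county holds one arm or both
- replaces the 90% with the power that those inputs deliver for that design

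This costs the rewording of one paragraph and a stated power that will probably be less favourable. The correction itself needs no added patients and no change to the conduct of the trial, which matters because the Trial status section says that enrolment began in December 2016.

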### Research hypothesis

We hypothesize that BSDOT, engaging patients with TB and village physicians, would allow patients to self-record their daily medications on a bracelet using a smartphone, and then send the data to the village physicians who could thus remotely monitor and document all medications and store patient records securely in the Cloud.

The study will be conducted in three phases: creation of a bracelet for patients with TB, design of a smartphone application capable of supporting medication adherence and bracelet software capable of recording tablet ingestion, and qualitative evaluation using a cohort of 400 patients with TB from both high- and low-resource areas and both urban and remote settings.

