## Methods/design

### Trial design

The study will be conducted in three phases: creation of a bracelet for patients with TB, design of a smartphone application capable of supporting medication adherence and a bracelet holding medication tablets, and performance of a qualitative evaluation of 400 patients with TB from both high- and low-resource and both urban and remote settings.

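### The sample-size paragraph gives no single coherent planning target: two constructs, two incompatible effects and two variance inputs, and at 1300 patients the 90% power does not hold for the 40% reduction

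*Protocol article*

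**What the plan says.** All the planning figures are in the Sample size section of the protocol article.

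- Endpoint: "the endpoint was the nonrecovery rate at the end of the trial".
- Control rate, first statement: a "percentage with nonadherence in the control arm of 30" per cent.
- Control rate and effect, second statement: "Using a treatment effect size of a 0.15 increase in the proportion of successful treatments over the 0.78 successful treatment rate for usual care".
- Effect, third statement: 1300 patients are needed "to detect a 40% reduction in the endpoint in the intervention arm".
- Other inputs: seven clusters per arm, two-sided 5% error, 90% power, an ICC of 0.1 and a coefficient of variation (CV) of 0.25.
- The 1300 is raised to 1365 for 5% missing endpoints.

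Under Outcomes and additional measurements, the WHO treatment result is primary and adherence is secondary.

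The third phase is described in two ways. Research hypothesis calls it a "qualitative evaluation using a cohort of 400 patients with TB", and Trial design gives it as "performance of a qualitative evaluation of 400 patients with TB from both high- and low-resource and both urban and remote settings". The Abstract and the phase 3 text under Study sites make the third phase a randomised trial, and its inclusion criteria require village residence in west Hunan.

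**The concern.** A sample size answers one question: how many patients are needed to detect this effect on this endpoint, given this between-cluster variation. Here each element is stated twice with different values. The endpoint is nonrecovery or nonadherence, with a control rate of 22% (1 minus 0.78) or 30%. The effect is 15 points or a 40% relative reduction. The between-cluster input is an ICC of 0.1 or a CV of 0.25.

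If the figures cannot all be true, a reader cannot tell which effect the trial was sized for, whether 90% power is real, or how to interpret a null result.

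**Working it through.** **The stated figure.** The last step reproduces: 1300 × 1.05 = 1365. The 1300 itself does not, as shown below.

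**Do the effects agree?**

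- 0.15 as absolute: non-success goes from 1 − 0.78 = 0.22 to 1 − 0.93 = 0.07, and 0.15/0.22 = 68%.
- 0.15 as relative: 0.78 × 1.15 = 0.897, so non-success goes from 0.22 to 0.103, and 0.117/0.22 = 53%.
- 0.15 taken off the 30%: 0.15/0.30 = 50%.
- A true 40% reduction: 0.22 × 0.6 = 0.132 (8.8 points), or 0.30 × 0.6 = 0.18 (12 points).

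No reading of the 0.15 gives 40%.

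**Can 1300 be recovered?** Let V = p0(1 − p0) + p1(1 − p1), d = p0 − p1 and f = (1.960 + 1.282)² = 10.507.

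- *With the ICC.* Patients per arm before clustering are n = fV/d². A design with c clusters per arm needs cluster size m = n(1 − 0.1)/(c − 0.1n), which has a solution only if 0.1n < c = 7.
- *With the CV* (Hayes-Bennett). Total N = 14V / [c·d²/f − 0.25²(p0² + p1²)], with c = 7, or c = 6 when one cluster per arm is kept as the small-sample allowance.

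| Pair | 2n, unclustered | 0.1n (must be < 7) | N at CV 0.25, c = 7 / c = 6 |
|---|---|---|---|
| 0.22 → 0.07 | 221 | 11.1 | 284 / 348 |
| 0.22 → 0.103 | 405 | 20.3 | 680 / 895 |
| 0.30 → 0.15 | 315 | 15.8 | 594 / 812 |
| 0.30 → 0.18 | 522 | 26.1 | 2576 / 8741 |
| 0.22 → 0.132 | 777 | 38.8 | 3834 / 13007 |

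At the stated ICC, no cluster size reaches 90% power for any pair. At the stated CV, no pair gives 1300. Trying 80% power, a one-sided test or seven clusters in total does not bring any pair within 3% of 1300 either. The nearest is 1215, for 0.30 → 0.18, and it needs a one-sided test that the section rules out.

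**Power at 1300.** With 14 clusters, m = 1300/14 = 92.86, and there are 650 patients per arm.

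- ICC 0.1: design effect = 1 + 91.86 × 0.1 = 10.19, and SE = √(V × 10.19/650).
- CV 0.25: SE = √{[V/92.86 + 0.0625(p0² + p1²)]/7}.

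Power is Φ(d/SE − 1.960). The lower end of each range below uses a noncentral t distribution with 12 degrees of freedom.

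Worked for 0.22 → 0.132, where V = 0.1716 + 0.1146 = 0.2862:

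- ICC: SE = 0.0670, d/SE = 0.088/0.0670 = 1.31, power 26% (t: 23%).
- CV: SE = √[(0.00308 + 0.00411)/7] = 0.0321, d/SE = 2.75, power 78% (t: 71%).

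| Pair | Power, ICC 0.1 | Power, CV 0.25 |
|---|---|---|
| 0.22 → 0.132 | 23-26% | 71-78% |
| 0.30 → 0.18 | 31-36% | 78-84% |
| 0.22 → 0.07 | 62-69% | above 99% |

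**Do the variance inputs agree?** A CV of k implies ICC = k²p/(1 − p). That is 0.0625 × 0.22/0.78 = 0.018 at 22% and 0.0625 × 0.30/0.70 = 0.027 at 30%. Both are well below 0.1.

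**The case against.** The strongest defence is that a target is stated: 1300, adjusted to 1365, for a 40% reduction at 90% power. That is right. A reader might infer that the plan defines no target at all, but the defect is that the stated target is not coherent.

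Four further inferences go beyond the text.

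- *Three endpoints.* Nonrecovery reads naturally as 1 minus treatment success, which leaves two constructs: non-success and nonadherence. The 30% also comes without a missed-dose threshold, so it cannot simply be equated with the secondary outcome's 5% rule.
- *1300 was derived from the 15-point effect and is therefore too small for 40%.* Since no pair tried reproduces 1300, the text does not show which effect produced it.
- *The unclustered totals show the problem.* The 221, 522 and 777 differ 3.5-fold, but all lie below 1300 and would suggest that it suffices. Only the clustered figures bear on this design.
- *400 is a rival randomised sample size.* Neither section says so. Both call it a qualitative evaluation, so power at 400 would describe a trial nobody proposes. What remains is an inconsistent description of phase 3.

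The defence can also say that the choice of effect is the sponsor's. It is: the 0.78 and 0.15 are tied to published rates and studies that are not shown here, so this review cannot choose between 0.15 and 40%. None of this makes the two effects compatible or restores 90% power for the 40% reduction.

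**Conclusion.** The point stands as a contradiction in the protocol's own figures. The 0.15 rise and the 40% reduction cannot both be the planned effect (68%, 53% or 50% against 40%), and the control rates of 22% and 30% belong to different constructs.

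For a 40% reduction, the stated 90% power is not reached at 1300 patients under either variance input: 23-36% at ICC 0.1 and 71-84% at CV 0.25, across both control rates. For 22% to 7%, power is adequate only if the CV is the right input.

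These results assume seven equal clusters per arm, as stated, 1:1 allocation, two-sided 5%, and the same ICC or CV in both arms. The Fig. 2 caption speaks of seven clusters in the province; if that were the total, power would be lower still.

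**What to change.** In the Sample size section:

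1. State one endpoint tied to the primary outcome: non-success, defined as 1 minus treatment success, with a control rate of 22%.
2. State one effect, chosen and justified by the sponsor: the 0.15 rise or the 40% reduction, not both. If it is the 0.15, say whether it is absolute.
3. Keep one between-cluster variance input, ICC or CV, and say why.
4. Label the 30% as a nonadherence figure that is not used for the primary outcome.
5. Restate the power that 1300 evaluable patients (1365 enrolled) in seven clusters per arm give for that target.

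Separately, reconcile the wording on 400 patients, including urban and high-resource settings, in Research hypothesis and Trial design with the randomised trial of 1365 village patients described under Study sites and Sample size.

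The cost is wording and one recalculation. The stated power becomes less favourable if the 40% reduction or the ICC of 0.1 is kept. If the ICC of 0.1 is kept, more patients in the same clusters will not restore 90% power for any pair above, so the restated power should be reported as it is.

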### Statistical analyses

Descriptive statistics will be calculated by reference to baseline data, to allow among-group comparisons. The baseline data will include age, sex, educational level, income, place of birth, smartphone access status, substance use status, distance from home to the nearest county hospital, disease status, and comorbidities. We will compare baseline patient characteristics between the two groups using the chi-squared test or adjusted logistic regression as appropriate. The significance level will be set at *p* ≤ 0.05.

Primary outcomes will be analyzed with the aid of a generalized mixed-effects model featuring both binomial distribution and logistic regression. Randomization (the intervention/control comparison) will serve as an independent variable. To accommodate the clustered design, we will treat clustering as a random effect. Potential confounders (age, sex, socioeconomic status, and other features) differing significantly between the intervention and control groups will be treated as fixed factors. Secondary outcomes (adherence to the medication regime, and education in terms of TB and QOL) will be explored with the aid of generalized linear mixed-effect models employing logistic or linear regression, as appropriate. Secondary outcome modeling will include baseline assessments as covariates. We will report all descriptive and inferential statistics with their 95% confidence intervals [23, 24]. We will treat TB treatment outcomes, treatment adherence, and self-reported adherence as enumerative data. Missing data will be handled by a complete case analysis which excludes individuals with missing data.

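### The 5% missing-data allowance multiplies by 1.05 instead of dividing by 0.95, so 1365 yields about 1296 evaluable patients, not 1300: a minor slip with negligible effect on power

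*Protocol article*

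**What the plan says.** The Sample size section of the protocol article gives the requirement before any allowance: "1300 TB patients would be required to detect a 40% reduction in the endpoint in the intervention arm", with two-sided alpha 0.05 and 90% power. It closes with the allowance: "The sample size was adjusted to 1365 assuming 5% missing endpoint data". No inflation formula is printed.

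The Statistical analyses section settles what happens to a patient without an endpoint: "Missing data will be handled by a complete case analysis which excludes individuals with missing data".

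**The concern.** An allowance for missing endpoints exists so that, after the expected loss, the analysis still has the number the calculation called for. Under a complete-case rule that means the enrolled number N must satisfy N × (1 − d) ≥ 1300, where d is the expected missing fraction of those enrolled. Multiplying the base by (1 + d) takes the fraction of the wrong number: it adds 5% of 1300, while the loss is 5% of everyone enrolled. The enrolment target then misses the plan's own evaluable number under the plan's own assumption.

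What is at stake is the consistency of three printed figures (1300, 5% and 1365) and the risk that the same rule is carried forward if the base is reworked. Power is not materially at stake, as the working shows.

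**Working it through.** **Inputs, all from the protocol article**

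- Evaluable patients required: 1300 (Sample size).
- Missing endpoints, d: 5% (Sample size).
- Stated target: 1365 (Sample size).
- Patients with missing data are excluded (Statistical analyses).
- For the power check (Sample size): seven clusters per arm, two-sided alpha 0.05, "an intra-cluster correlation coefficient (ICC) of 0.1 was estimated as a mid-range value", a coefficient of variation of 0.25, and the effect assumptions, including "a 0.15 increase in the proportion of successful treatments over the 0.78 successful treatment rate for usual care" and a 40% reduction in the endpoint.

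**Step 1. Reproduce the stated figure.** 1300 × (1 + 0.05) = 1365.0, an exact match. The multiplication is inferred from this match.

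**Step 2. Evaluable patients at the stated loss.** 1365 × (1 − 0.05) = 1296.75, that is 1296 or 1297 whole patients. Shortfall: 1300 − 1296.75 = 3.25, and 3.25 / 1300 = 0.25%. This step holds however 1365 was reached.

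**Step 3. The number that meets the requirement.** 1300 / (1 − 0.05) = 1368.42, rounded up to 1369. Check: 1369 × 0.95 = 1300.55. The difference from the stated target is 1369 − 1365 = 4 patients.

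**Step 4. The loss that 1365 does cover.** (1365 − 1300) / 1365 = 65 / 1365 = 4.76%.

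**Step 5. Effect on precision with 14 clusters and ICC 0.1.** Design effect = 1 + (m − 1) × 0.1, with m patients per cluster.

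- N = 1300: m = 92.86, design effect 10.186, effective N = 1300 / 10.186 = 127.63.
- N = 1296.75: m = 92.63, design effect 10.163, effective N = 1296.75 / 10.163 = 127.60.

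The loss is about 0.03 of an effective patient. With the number of clusters fixed, a few patients more or fewer per cluster barely matter.

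**Step 6. Effect on power.** The coefficient-of-variation formula for a cluster trial is: power = Φ(|q1 − q2| / √v − 1.96), with v = {[q1(1 − q1) + q2(1 − q2)] / m + k²(q1² + q2²)} / (7 − 1), k = 0.25 and m = N / 14.

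| Scenario | Power at 1300 | Power at 1296.75 |
|---|---|---|
| Non-success 0.22 to 0.132 (40% reduction), CV formula | 0.7194 | 0.7190 |
| 0.30 to 0.15, CV formula | 0.9449 | 0.9448 |
| Success 0.78 to 0.93, two-proportion test with the ICC 0.1 design effect | 0.6761 | 0.6760 |

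For the first row: [0.1716 + 0.1146] / 92.86 = 0.003082; 0.0625 × (0.0484 + 0.0174) = 0.004114; v = 0.007196 / 6 = 0.001199; 0.088 / 0.03463 − 1.96 = 0.581; Φ(0.581) = 0.719.

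The change was below 0.05 percentage points in every scenario tried. The levels of power differ widely between rows because the inputs in the Sample size section do not describe one scenario. That is a separate matter, taken up in the verdict.

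**The case against.** The best case for leaving 1365 alone has four parts.

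*The figure is right at its stated precision.* 1365 retains 1300 at 4.76% missing, which rounds to 5%. Both the 5% and the 1300 look like round planning numbers, so a correction of 4 patients is finer than either supports. This limits the importance, and it stands to that extent. It does not remove the slip: at the 5% the plan states, 1365 falls short of 1300, and division by 0.95 gives 1368 or 1369 whichever way it is rounded.

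*Some of the 5% may not be missing at all.* Under Outcomes and additional measurements, death, loss to follow-up and non-evaluation are themselves categories of the primary outcome, so many patients without a final result could still be classified. This stands as a caution: how many would really be excluded cannot be read from the article, and the 1296 is conditional on the plan's assumption. But the plan itself posits 5% missing endpoints and itself excludes patients with missing data, and the check only holds it to those two statements.

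*Nothing follows from it.* On power this is correct. A reader might infer that the trial loses its 90% power through this shortfall. The article's figures do not support that: moving from 1300 to 1296.75 changes power by less than 0.05 percentage points.

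*Correcting 1365 lends credit to 1300.* This is a fair warning, and it governs how the fix must be worded. A further step to 1370 for equal arms is likewise not called for: in a cluster randomized trial the patient numbers per arm need not be equal.

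**Conclusion.** The slip is real and minor. Under the stated complete-case analysis and the stated 5% loss, 1365 enrolled gives about 1296 evaluable patients, 3 to 4 fewer than the 1300 the plan says it needs, or 0.25%. The conclusion rests on two readings: that 5% is the missing fraction of enrolled patients, and that patients counted as missing leave the primary analysis. That 1365 came from multiplying by 1.05 is inferred, but the shortfall does not depend on it.

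Two stronger inferences are not supported. One is that the slip weakens the trial's power; Steps 5 and 6 show that it does not. The other is that changing 1365 to 1369 would make the sample size sound. The base of 1300 did not reproduce from the stated inputs. With ICC 0.1 and seven clusters per arm, the fixed-cluster formula needs n × 0.1 below 7, where n is the individually randomized number per arm. The smallest n among the pairs of rates tried was 114 (0.78 to 0.93), giving 11.4, so 90% power was out of reach for every pair. The coefficient-of-variation formula, applied to the adverse-outcome rate, gave totals from about 348 (0.22 to 0.07) to about 13,000 (0.22 to 0.132). That is a larger and separate question, which this point neither settles nor depends on.

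**What to change.** Change one sentence in the Sample size section, in either of two ways:

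- keep 1365 and state that it yields about 1296 evaluable patients at 5% missing, or that it covers 4.8% missing; or
- give the inflated figure as 1300 / 0.95 = 1369.

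The first costs no patients, the second costs 4. Whichever is chosen, the text should not suggest that the base has thereby been confirmed. If 1300 is recalculated, divide the new base by (1 − 0.05), so that the same slip is not carried into the new target.
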